### Sample size

Sample size calculation is based on a study by Camilleri:A placebo-controlled trial of prucalopride for severe chronic constipation [J]. N Engl J Med, 2008, 358 (22): 2344–2354 [11]. After drug treatment, the average defecation rate of patients with functional constipation was 2.6 times per week, with a standard deviation of 2.2. Furthermore, there was a 1.4-fold difference in the clinical effects between the drug and the placebo. Therefore, based on this study along with our preliminary test, the mean defecating frequency is 4.0 after acupuncture treatment, with a standard deviation of 3. To detect this difference, we need a minimum total sample size of 213 [71 for each group (α = 0.05, β = 0.10)] [12]. To allow for a loss of 15%, a total sample size of 243 (81 for each group) is required.

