### Outcome measures

All of the participants in this trial will be asked to update constipation diaries from 1 week before randomization to 8 weeks after randomization. Only when they are eligible in the baseline phase for this study will the participants be asked to make diary entries from 0 to 8 weeks after randomization.

The primary outcome in this trial is the number of defecating events per week at baseline and at the 2nd, 4th and 8th week after randomization (Table 1 and Figure 2). Secondary outcomes include the following five aspects: shape and properties of stool, intensity of defecating difficulty, Patient Assessment of Constipation Quality of Life (PAC-QOL), MOS item Short Form health survey (SF-36), Self-Rating Anxiety Scale (SAS), and Self-rating Depression Scale (SDS). The first three of the secondary outcomes will be measured at baseline and at the 2nd, 4th and 8th week after randomization. The other secondary outcomes will be measured at baseline and at the 2nd and 4th week after randomization, although SF-36 will be measured only before randomization and 4 weeks after randomization. Additionally, the time of the first spontaneous defecation (from the end of the first intervention to the first spontaneous defecation) will be recorded.

**Table 1 T1:** Trial process

	**Baseline**	**Treatment**			**Follow-up**
**Time**	−1w	0w	2w	4w	8w
**Assessment**		1st	2nd	3rd	4th

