### Trial evaluation

The trial evaluation will include patient compliance and the ratio of dropouts or withdrawals, which will be measured at the 4th week after randomization, and their reason will be recorded in time.

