### Statistical analysis

Statistical analyses will be undertaken by the Department of Epidemiology and Biostatistics, School of Public Health, Tongji Medical College, Huazhong University of Science and Technology. Baseline characteristics of the subjects will be described by descriptive analysis and analyzed by analysis of variance, *χ*^2^-test, and others. With regard to the effects of intervention, the *χ*^2^-test will be applied to compare frequencies between groups, such as the number of defecating times per week; analysis of variance will be performed for comparison of continuous parameters between the groups (α = 0.05). All of the analyses will be based on both an intention-to-treat analysis (ITT) and a treated-per-protocol analysis (TPP).

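### The tests named for the repeated outcomes make no use of a leaver's earlier diary counts, so unless the full plan adds imputation the ITT comparisons at weeks 4 and 8 are not secured

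*Protocol article*

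**What the plan says.** The Statistical analysis section gives the chi-square test this role: "test will be applied to compare frequencies between groups, such as the number of defecating times per week". For continuous outcomes it says "analysis of variance will be performed for comparison of continuous parameters between the groups (α = 0.05". It names no other method for effects. On analysis sets it says "All of the analyses will be based on both an intention-to-treat analysis (ITT) and a treated-per-protocol analysis (TPP".

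The Outcome measures section defines the primary outcome as the "number of defecating events per week at baseline and at the 2nd, 4th and 8th week after randomization", and the diary covers the whole period: "All of the participants in this trial will be asked to update constipation diaries from 1 week before randomization to 8 weeks after randomization".

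The Sample size section gives "71 for each group (α = 0.05, β = 0.10") and then "To allow for a loss of 15%, a total sample size of 243 (81 for each group) is required". The Trial evaluation section records dropouts and withdrawals with their reasons, "which will be measured at the 4th week after randomization".

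**The concern.** The plan has repeated measurements, expects a noticeable loss, promises ITT, and names only tests that need a value at the time point compared. Someone who leaves in week 3 has diary counts up to that point, but those counts say nothing in a week-4 or week-8 chi-square test or one-way analysis of variance unless a value is imputed.

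The arms also differ in ways that could make loss unequal. One receives current at the tolerance threshold over 16 sessions, one a weak current over 16 sessions, and one takes tablets. If poor responders leave one arm more often, the mean of those who remain is too favourable. A result labelled ITT would then carry the selection that ITT is meant to prevent. The weekly count and the visit-based secondary outcomes are exposed in the same way.

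**Working it through.** **Inputs.** From the Sample size section: means 2.6 and 4.0 per week (difference 4.0 − 2.6 = 1.4), SDs 2.2 and 3, α 0.05, power 90%, 71 per group, 15% loss, 81 per group. Assumed, because the article is silent: two-sided testing, loss by arm, its dependence on response, and a within-patient correlation ρ between weeks of 0.5 to 0.7.

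**1. The plan's own figures.** n = 2·SD²·(1.960 + 1.282)²/1.4².
- Simple average SD of (2.2 + 3)/2 = 2.6: 2 × 6.76 × 10.51/1.96 = 72.5, so 73 per group.
- Separate SDs 2.2 and 3: (4.84 + 9) × 10.51/1.96 = 74.2, so 75.
- Three-group F test with means 2.6, 4.0, 4.0 and SD 2.63: 69.

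The stated 71 lies among these. Then 71 × 1.15 = 81.65, given as 81. This point disputes neither figure.

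**2. What each named test does with a missing week-4 or week-8 value, absent imputation.**

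| Method | Participant with no value at that visit |
|---|---|
| Chi-square test | not counted |
| One-way analysis of variance | not counted |
| Classical repeated-measures analysis of variance | dropped if any visit is missing |
| Mixed model on all weeks | kept, through the weeks observed |

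**3. Numbers and power.** With 15% missing at a visit, 81 × 0.85 = 68.85, about 69 per group. For a two-sided test of 1.4 with SDs 2.2 and 3, power is 87.8% at 69, 88.7% at 71 and 92.3% at 81. The last is an upper bound on what a model using partial data could recover.

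**4. Size of a possible bias at week 4.** In one arm, the shift in the observed mean is (share lost) × (mean of stayers − mean of leavers). Take SD 3. Let loss after week 2 in one arm depend on the deviation d of the week-2 count from its mean. Let loss in the other arm be random, which adds no bias.

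- *Stronger dependence:* logit P(leave) = −2.0 − 0.5d. Loss is 19.0%. Stayers average d = +0.649 and leavers d = −2.767. The expected week-4 deviation is ρ times these. Shift: 0.5 × 0.649 = 0.32 and 0.7 × 0.649 = 0.45 (0.455 before rounding d), which is 23% and about 33% of 1.4. Check: 0.190 × 0.5 × (0.649 + 2.767) = 0.325.
- *Weaker dependence:* slopes 0.1 to 0.2 with the intercept set for 15% loss. Shift from 0.07 (slope 0.1, ρ 0.5) to 0.18 (slope 0.2, ρ 0.7), which is 5% to 13% of 1.4.
- *Simple cross-check:* the same stayer–leaver gap in both arms, so shift = (difference in loss) × gap. Loss of 10% v 20% and gaps of 0.5 to 2.0 give 0.05 to 0.20. Loss of 5% v 25% gives 0.10 to 0.40.
- *No bias:* with equal loss and an equal gap, or with loss unrelated to response, the shift is zero.

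**5. What the alternative does.** In simulations of the stronger rule, a likelihood model on the weekly counts came within 0.04 of the true difference, whether that was 0 or 1.4. This is expected: the simulated loss depends only on observed counts, which is the model's own assumption.

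**The case against.** The strongest objection is that the article nowhere says how missing values are handled. It does not say that tests are run separately at each visit, that the analysis of variance is one-way, or that people without a value are left out. Imputation is compatible with its wording, and a condensed article may leave this to the full protocol or SAP. The promise of ITT, if anything, points away from deliberate exclusion. This stands. Silence on missing data is not the finding, and the point has to be conditional. It still rests on something stated, namely the methods named. Reading the analysis of variance as the classical repeated-measures kind does not help, because that drops anyone with a missing visit.

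Three further objections stand in part.
- Inflating the sample size for loss is routine and does not show that leavers will be excluded.
- Someone leaving in week 3 would still enter the week-2 comparison, and someone leaving in week 6 would enter weeks 2 and 4. All participants are already asked to keep the diary to week 8. The gap therefore concerns the later visits and the use made of the data.
- The sentence on analysis of variance covers continuous outcomes, while the weekly count is the example given for chi-square. Both tests share the limitation. The sizes above are mean differences because the plan's target of 1.4 is one.

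Finally, the article gives no loss by arm, so unequal loss is plausible but not shown.

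**Conclusion.** The point holds in conditional form. The named tests do not use partial follow-up, so without imputation in the full plan the week-4 and week-8 ITT comparisons would rest on those with data at that visit.

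A reader might infer that the plan runs separate visit-by-visit tests and that its ITT analysis is in fact a completer analysis. The document states neither, and that reading should not be reported as fact.

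The size is about 0.07 to 0.46 defecations per week at week 4, or 5% to 33% of the planned 1.4. It rests on response-related loss of 15% to 19% in one arm only, SD 3 and a between-week correlation of 0.5 to 0.7. The upper end needs leavers to be about 1.7 to 2.4 per week below stayers, which is large beside planned means of 2.6 and 4.0. With equal loss unrelated to response the bias is about zero. What remains then is a modest loss of power, to about 88% at 69 per group against at most 92% at 81. The case for change is that a better method is available on data already collected.

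**What to change.** For the ITT analysis of the weekly count, replace the chi-square or analysis-of-variance comparison with one repeated-measures mixed model, linear or count-type. Include baseline and all collected diary weeks for every randomised participant, and read the arm contrast at the chosen week from that model. Add one sensitivity analysis that sets leavers to their own baseline count for the weeks after they leave.

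The cost is a change of wording and modest analyst time. No visits, tests or participants are added, since the diary already runs to week 8. The downside is that the model assumes loss is explained by the observed counts (missing at random). The sensitivity analysis probes that assumption. If the full plan already specifies imputation or such a model, the article's Statistical analysis section only needs to say so.

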### Randomization and blinding

The participants will be randomly assigned to three groups through complete randomization at a 1:1:1 ratio equally among the three centers: high current intensity group, low current intensity group, and mosapride citrate control group. Therefore, each group in each center will have 27 participants. The randomization sequence will be generated using R2.0 software. A designated researcher will prepare the assignments in opaque envelopes in sequence.

The acupuncturists will only know of the grouping scheme just prior to the treatment to ensure that the trial will be as blinded as possible. The researchers will not be permitted to predict a patient’s assignment or change it after the patients are randomized. Blinded evaluation (the curative effect will be evaluated by a third party who does not know the grouping) and blinded statistical analysis will be emphasized during the data collection and analysis stage.

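### The tests named for treatment effects use neither the baseline defecation count nor centre, so precision is given up; the analysis is not thereby biased

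*Protocol article*

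**What the plan says.** The Statistical analysis section names two tests for treatment effects. A chi-square test is to compare frequencies, with weekly defecations given as the example. For the rest, "analysis of variance will be performed for comparison of continuous parameters between the groups". Group is the only factor mentioned. Baseline characteristics are described and compared between groups by analysis of variance, chi-square and other tests; no other use of baseline data is stated.

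Under Outcome measures, "All of the participants in this trial will be asked to update constipation diaries from 1 week before randomization", and the weekly count is listed at baseline and at weeks 2, 4 and 8. Table 1 shows that PAC-QOL, SF-36, SAS and SDS also have a pre-treatment value.

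Under Randomization and blinding, the three arms are allocated 1:1:1, equally among three centres: "Therefore, each group in each center will have 27 participants". The same paragraph calls the method complete randomization, which by itself would not guarantee that number in every cell.

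**The concern.** A patient's own baseline count is a natural predictor of the later count. If it is left out of the effect analysis, variation between patients that could have been explained stays in the error term, and any chance imbalance at baseline stays in the estimate. A significance test of baseline balance does nothing about either. Centre is similar: where allocation is balanced within centre, an analysis without centre counts between-centre variation as noise although the design has removed it from the comparison.

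At stake is power, and by the plan's own figures there is little to spare. The calculation asks for 71 evaluable per arm, while 81 enrolled less the stated 15% loss leaves about 68.

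**Working it through.** **Inputs from the Sample size section.** Comparator: "the average defecation rate of patients with functional constipation was 2.6 times per week, with a standard deviation of 2.2". Acupuncture: "the mean defecating frequency is 4.0 after acupuncture treatment, with a standard deviation of 3". The difference is 4.0 − 2.6 = 1.4. Target: "71 for each group (α = 0.05, β = 0.10". Enrolment: "To allow for a loss of 15%, a total sample size of 243 (81 for each group) is required". Sidedness is not stated; two-sided is assumed. Neither r nor a centre effect is given, so both are assumed over ranges.

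**The plan's own figure.** The unadjusted two-sample formula is n = 2[SD(1.96 + 1.2816)/1.4]². With the mean of the two SDs, (2.2 + 3)/2 = 2.6, n = 72.5, or 73 per arm. This is within 2 of the stated 71, so the stated size is consistent with an unadjusted comparison of means.

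**Power without adjustment.** Evaluable per arm: 81 × 0.85 = 68.85, taken as 68. The standard error (SE) of the difference is √[(3² + 2.2²)/68] = √(13.84/68) = 0.451. Then 1.4/0.451 = 3.10, and 3.10 − 1.96 = 1.14, a power of about 87%.

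**Adjustment for baseline.** Residual variance is multiplied by 1 − r², taking the same r in each arm, so SE = 0.451 × √(1 − r²). Power is from the Welch test:

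| assumed r | variance cut | SE | power |
|---|---|---|---|
| 0 | 0% | 0.451 | 87% |
| 0.1 | 1% | 0.449 | 87% |
| 0.2 | 4% | 0.442 | 88% |
| 0.3 | 9% | 0.430 | 90% |
| 0.5 | 25% | 0.391 | 94% |
| 0.6 | 36% | 0.361 | 97% |

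The equivalent increase in sample size is 1/(1 − r²): 1.10 at r = 0.3 and 1.56 at r = 0.6.

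**Centre.** Let ICC be the share of total variance lying between centres. With three centres, the pooled within-arm variance contains on average about two thirds of the between-centre variance. Under exact balance within centre, the unadjusted SE is therefore too wide by the factor √{[(1 − ICC) + (2/3)ICC]/(1 − ICC)}:

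- ICC 0.05: √(0.9833/0.95) = 1.017, or 1.7%.
- ICC 0.10: √(0.9667/0.90) = 1.036, or 3.6%.

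A simulation of two arms with 27 per arm in each of three centres (SD 2.63, the root mean square of 2.2 and 3) agrees. The mean SE is 0.410 unadjusted against 0.403 adjusted at ICC 0.05, and 0.405 against 0.391 at ICC 0.10. At ICC 0.10 the type I error is about 0.043 unadjusted and 0.051 adjusted, and power for 1.4 is about 0.936 and 0.946. With 8,000 null runs, the simulation error of a type I rate near 0.05 is about √(0.05 × 0.95/8000) = 0.0024, so the third decimal should not be pressed.

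**The case against.** The best defence is that a short statistical paragraph in a journal article does not settle model terms. It nowhere says that the analysis is unadjusted, analysis of variance can carry a centre factor, and covariates are commonly left to a fuller plan. That stands in part. It would be wrong to say that the plan excludes adjustment, or that the analysis of variance is one-way: a reader might infer either, but the text says neither. What remains is that the article does choose its tests. A chi-square test of the weekly count takes no baseline covariate, and the one stated use of baseline data is description and testing.

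Four further limits stand.

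- The analysis-of-variance sentence does not govern the primary outcome, which goes to chi-square. The power figures above therefore show what adjustment is worth in a comparison of means; they do not measure the loss from the test named for that outcome. That chi-square suits a weekly count poorly is a separate and more serious weakness.
- The gain from baseline rests wholly on an assumed r. A reader might take the upper end, equivalent to 56% more patients, as the trial's loss. Nothing in the document supports that, and at r of 0.1 to 0.2 the gain is slight.
- That the standard errors ignore centre might suggest invalid inference. Under balanced allocation the error runs the safe way: intervals slightly too wide, type I error not inflated, estimate unbiased.
- Exact within-centre balance is itself in doubt, since complete randomization and 27 per cell do not fit together. If allocation is unrestricted, the standard-error argument for centre weakens; the baseline argument does not.

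**Conclusion.** The point holds as one of efficiency. The tests named use neither the baseline count nor centre, although the first is collected and the second is meant to be balanced.

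Baseline is the main part. On the plan's means and SDs, two-sided testing and 68 evaluable per arm, even r = 0.3 would bring a comparison of means back to about the 90% power intended. The size cannot be fixed from the document because r is not reported. Centre is minor: one or two points of power at most within the range considered.

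The document does not support a charge of bias or of an invalid analysis. The change is worth making because it improves on the tests named and uses data already collected.

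**What to change.** Prespecify, before unblinding, a primary model of the weekly defecation count on group, baseline weekly count and centre, in place of the chi-square test. ANCOVA, or a count model such as the negative binomial, would serve. Analyse PAC-QOL, SF-36, SAS and SDS by ANCOVA, each with its own baseline value and centre. Keep an unadjusted comparison as a sensitivity analysis. State also whether allocation was restricted within centre, so that the reason for the centre term is clear.

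The cost is wording in the analysis plan; every covariate is already recorded. The Trial status section reports 123 of the planned 243 recruited by 15 March 2013, with recruitment continuing, so at that date the change could be made in advance. The same adjustment chosen after the data have been seen would invite doubts about selective analysis.

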## Discussion

Acupuncture has the characteristic of integral two-way adjustment and can regulate multiple body function disorders, such as constipation and diarrhea. The selected points can be the same or different. However, the quality of past studies has been poor, e.g., small sample size, no description of the methods for randomization, and no standardized acupuncture protocol, which may lead to performance bias. The project “Two-way adjusting effects of acupuncture for functional bowel disease and its mechanism” is sponsored and financed by the ‘973 Program’ administered by the Ministry of Science and Technology of China, which is the most important basic research program based on clinical practice. Twelve scientific institutes participate in this project. A multicenter, randomized, parallel controlled trial has been designed to confirm the effectiveness of acupuncture for functional constipation and functional diarrhea, and to explore the possible relationship of stimulus quantity and their effects. This article is just one part of this trial for addressing problems related to constipation.

The rationale behind the study of electro-acupuncture intensity is that different parameters of stimulation may cause different therapeutic effects for the same disease; the same parameters of stimulation may also bring different effects for different diseases. That is, some dysfunction may need mild stimulation, while others may need strong stimulation. In addition, different subjects, even different parts of one subject, can have different levels of sensitivity and acceptability. Therefore, the currents applied in the high- and low-intensity groups cannot be constant values, but instead, variable ranges. Based on the preliminary study, using an alternating wave of 2/50 Hz, the current reaching the patients’ tolerance threshold value ranges from 1.0-1.8 mA, while the current in the low-intensity group is relatively weak; a 0.2-0.7 mA current can be clearly perceived by the participants.

As for the rationale of acupoint selection, we screened acupoints through a systematic review of ancient books, acupuncture textbooks, and published articles. Meetings were held to further screen for a standardized acupuncture protocol and reach consensus among acupuncture experts in China. Based on the theory of acupuncture, Back-Shu and Front-Mu points (short for Shu-Mu points), which are located in the lower back or abdomen of the body, are the classic combination for the treatment of internal organ disease. Additionally, Hepoint (Quchi, LI11) and Lower Hepoint (Shangjuxu, S37) of the large intestine meridian are also positive points, which are respectively situated in the upper and lower limbs of the body. Nei Jing states: ‘He points are the best points to treat internal organ’s disease.’ However, our preliminary results have indicated that the effect of Shu and Mupoints in rats mainly excite gastrointestinal motility, while the effect of acupuncture in either Quchi or Shangjuxu is characterized by inhibiting motility. Therefore, the purpose of this study is to further validate the effect of acupuncture in Hepoints (Quchi and Shangjuxu) on functional constipation, as well as the relationship between the stimulation intensity and the resulting effect.

In this trial we are using mosapride as a positive control group rather than sham acupuncture as a negative control group. This setting is mainly based on the fact that any surface stimulation at acupoints, such as acupressure, can cause a physiological reaction or effect [13,14]. Thus, it is difficult to set a real non-active control for clinical acupuncture trials. As for mosapride, it is a gastroprokinetic agent that acts as a selective 5HT4 agonist. Mosapride accelerates gastric emptying and is used for the treatment of acid reflux, irritable bowel syndrome and functional dyspepsia [15]. Thus, mosapride also has the potential to treat functional constipation [16]. We therefore chose mosapride citrate as a positive drug control.

This study will provide significant evidence for the application of acupuncture in functional constipation and will be the first to identify a suitable parameter of stimulation for treatment.

